## Discussion

The number of PWD worldwide is projected to triple to 131.5 million by 2050 [53]. As the disease progresses, the self-care ability of PWD will gradually reduce or be lost. The family caregivers of PWD face many challenges since they need to balance the caregiving tasks with other demands, such as their career and social life. The continuous stress of caregiving results in different physical and psychological comorbidities among these caregivers. In a previous study, the stress-related symptoms including depression and anxiety were found in 45% to 85% of caregivers of PWD, respectively [54, 55]. Improving the psychological well-being of family caregivers is becoming important in dementia care.

MBCT aims to help caregivers develop accepting and nonjudgmental attitudes to caregiving, resulting in stress reduction and also promoting the well-being of the family caregivers. The MBCT does not emphasize any changes in personal thoughts or feelings, but assists and teaches the caregivers to accept their negative emotions and keep them at a distance. This unique nature of mindfulness may empower the caregivers who are facing everyday stress. The improvement in the mental health of the family caregivers could maintain their sustainability in providing daily care to PWD for a longer period of time, delay the institutionalization of PWD, and also decrease the cost of care to society.

The improvement in the mental health of the family caregivers may also extend to PWD. The mindfulness practice can help the caregiver facilitate their responses to external stimuli, such as the behavioral problems of PWD, in a less reactive and impulsive way. In our previous feasibility study, a number of caregivers found that their acceptance of the behavioral problems (e.g., wondering, asking repeated questions) of the PWD was increased after practicing mindfulness and they showed more patience in managing the caring problem [16]. Being more mindful, an example caregiver shared that she could avoid arguing with the PWD but be silent for a while when her mother asked her questions repeatedly, thus resulting in a more harmonious relationship with the PWD and less behavioral problems for the PWD. The interaction of the caregivers and PWD could affect the severity of the BPSD [56]. Since only a few previous studies have explored the use of mindfulness in the caregivers, this is the first study that will also look at the impact on the BPSD of the PWD.

## Limitations

We are conducting this study in nongovernmental organizations offering support for the family caregivers, which may limit the ability to generalize the findings to all community-dwelling caregivers. There is also a chance of bias since the participants are aware of the intervention. Thus, the level of mindfulness will be measured to understand the mediating effect or active components of the MBCT contributing to any significant benefits for the participants.

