### Hypotheses of the study

Participants in the intervention group will have better improvement than the control group after the seven-session, 10-week modified MBCT intervention immediately after the intervention (T1) and/or at 6-month follow-up (T2) in terms of the following hypotheses: 1) significantly greater reduction of stress (primary outcome); and 2) significantly greater improvement in the secondary outcomes, namely depression, anxiety, resilience, burden, health-related quality of life, and the behavioral and psychological symptoms of the care recipient.

In addition, there are two hypotheses to facilitate the explanation of the positive changes in the modified MBCT group: 1) there will be significant positive correlations between the levels of mindfulness of the caregivers (total score of five facets of mindfulness) and the improvement in their stress, depression, anxiety, burden, resilience, health-related quality of life, and/or behavioral and psychological symptoms of the care recipient; and 2) increased use of all facets or individual facets of mindfulness skills of family caregivers will be significantly and positively correlated with the improvements in their psychological outcomes (stress, depression, anxiety, burden, resilience, and/or health-related quality of life).

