### Randomization and blinding

The eligible participants will be randomized into the two groups (modified MBCT or social interaction and routine education (SIRE)) following an allocation concealment mechanism. To ensure equal sample sizes (1:1) in the modified MBCT and SIRE, the allocation of participants will be performed using a block randomization method and computer-generated numbers by an independent research assistant who will not be involved in the recruitment, assessment, or delivery of the intervention. The procedure and treatment allocation will be blinded to the investigators and outcomes assessors. The interventionists will be blinded to all the assessment results. The subjects will be told about their group assignment during the first session of the intervention via a sealed envelope.

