### Outcome measurement

A variety of outcomes (described below) will be measured at baseline (T0), immediately after the intervention (T1), and at 6-month follow-up (T2). The FFMQ will be measured in the intervention group only and the baseline measurement will be conducted at the end of the third session (the mid-point of the intervention) when they have learned most of the basic skill and principle of mindfulness [28], followed by measurement immediately after the intervention (T1) and at 6-month follow-up (T2). The previous study showed that the participants’ level of mindfulness started to increase after the mid-point of the intervention, and the remaining sessions after the mid-point will further help the participants to cultivate a mindfulness attitude [29]. All assessments will be carried out by independent outcomes assessors who will be blinded to the group assignments. Sociodemographic data of the subjects will be obtained at baseline (before randomization and within 2 weeks before the implementation of the intervention) to assess the comparability of the groups and thus external validity of the results. Information such as caregiver relationships, time of caring for PWD, employment status, use of caring service, and so on, will be obtained.

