#### Level of mindfulness

Since the primary objective of the modified MBCT program is to help the participants cultivate a mindfulness attitude, the level of mindfulness will be measured as the process indicator using the Chinese version of the Five Facets Mindfulness Questionnaire Short Form (FFMQ-SF) [46], which has been commonly used to measure mindful awareness in mindfulness studies [47]. It is a self-report questionnaire measuring the five facets of mindfulness which includes observing, describing, acting with awareness, nonjudging of and nonreactivity to inner experience (e.g., “I’m good at finding words to describe my feelings”). The higher the score, the higher level of mindfulness. The Chinese version of the FFMQ-SF was tested in community-dwelling Chinese adults (*n* = 230) and clinical patients with significant psychological distress (*n* = 156) [46]. The results showed good test-retest reliability of 0.82 and a high internal consistency Cronbach’s alpha 0.80 in the community and clinical samples [46].

The adherence rate and frequency of mindfulness practice will be assessed based on the participants’ attendance in the weekly mindfulness training sessions in the experimental group. Additionally, they will be instructed to record the frequency and duration of mindfulness practice at home during the previous week. They will also be asked to write down weekly mindfulness practice duration (hours) and rate their overall level of adherence to their practice regimen on a 10-point scale from 0 (non-compliance) to 10 (full compliance) based on the following question: ‘Did I comply with the practice regimen in the past 7 days?’. This information will be collected weekly after the mindfulness program and will continue to be collected bi-weekly during the follow-up period. The reasons for any drop-out of each participant will also be recorded.

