The Pearson’s correlation coefficient (*r*) (or Spearman’s correlation coefficient, as appropriate) will be adopted for the following variables to examine their correlations:The FFMQ total score as the independent variable and the outcome measurements including mean scores of stress, depression, burden, and anxiety as the dependent variables.The subscale (each facet) of the FFMQ score as the independent variable and the outcome measurements including mean scores of stress, depression, burden, and anxiety as the dependent variables.The duration of mindfulness practice as the independent variable and the level of mindfulness as the dependent variable.

The degree and pattern of missing data will be analyzed using SPSS Statistics Missing Values. If the missing value is a small amount (< 20%) and randomly distributed, the last observation carried forward (LOCF) method will be adopted to replace the missing data [50, 51]. However, if the missing values are not randomly distributed, multiple imputations will be adopted. This will create several different plausible imputed datasets and the results obtained from each of the sets will be appropriately combined [52].

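### Mindfulness is measured only in the MBCT arm, so its mediating effect cannot be estimated, the planned group × time test on FFMQ cannot be fitted, and the measurement does not answer participant-awareness bias

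*Protocol article*

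**What the plan says.** The Limitations section discloses a bias, "There is also a chance of bias since the participants are aware of the intervention", and responds in the next sentence: "Thus, the level of mindfulness will be measured to understand the mediating effect or active components of the MBCT".

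Four other sections of the protocol article fix what can be done with that measurement:

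- **Outcome measurement:** "The FFMQ will be measured in the intervention group only". The first measurement is late: "the baseline measurement will be conducted at the end of the third session (the mid-point of the intervention". It is repeated at T1 and T2.
- **Level of mindfulness:** "It is a self-report questionnaire measuring the five facets of mindfulness".
- **Randomization and blinding:** "The subjects will be told about their group assignment during the first session of the intervention via a sealed envelope". Every FFMQ is therefore completed by someone who knows their arm.
- **Hypotheses and Data analysis plan:** "there are two hypotheses to facilitate the explanation of the positive changes in the modified MBCT group". Both are framed as correlations, and the planned analysis is a Pearson or Spearman correlation with "The FFMQ total score as the independent variable and the outcome measurements including mean scores of stress, depression, burden, and anxiety as the dependent variables". The Data analysis plan also lists FFMQ, as the process indicator, among the variables to be tested for group, time and group × time effects.

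**The concern.** Mediation of a randomised effect has two parts: arm must change the mediator, and the mediator must be related to the outcome given arm. With no FFMQ in SIRE, the first part is absent from the data. A high or rising FFMQ in MBCT cannot be told apart from what seven sessions of group contact would give anyway. SIRE exists to control for that contact, but the control is lost for the mechanism question.

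The *Thus* is a separate difficulty. FFMQ and PSS are both reported by the same caregivers, who know their programme. Expectation can move both, so their correlation may be a product of the bias it is introduced to address.

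At stake is what the report may say about mechanism: whether mindfulness can be put forward as the active ingredient, and whether readers are led to give expectation less weight than the design warrants.

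**Working it through.** The plan gives no figure on this point to reproduce. The check is one of identification, with two illustrations whose inputs are assumptions.

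**1. Is the arm → mindfulness path in the data?**
Inputs: 50 per group (Sample size); FFMQ in MBCT only (Outcome measurement). Caregivers with FFMQ: up to 50 in MBCT and 0 of 50 in SIRE. Among those with a value, arm is constant, so the design matrix [1, arm] has rank 1 where 2 is needed. The arm effect on FFMQ is not estimable. For the same reason, the group and group × time terms for FFMQ in the Data analysis plan cannot be fitted. The time axis does not match either: that model uses T0, T1 and T2, and FFMQ has no T0.

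**2. What does the missing arm leave open?**
Indirect effect = a × b, where a = FFMQ gain in MBCT − FFMQ gain in SIRE, and b = the mindfulness–stress slope. Assume an MBCT gain of 0.5 SD and b = −0.4.

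| Unobserved SIRE gain (SD) | a | a × b |
|---|---|---|
| 0 | 0.50 | −0.20 |
| 0.25 | 0.25 | −0.10 |
| 0.50 | 0 | 0 |
| 0.75 | −0.25 | +0.10 |

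All four rows fit the same MBCT-arm data, and even the sign is open. In this trial the MBCT gain itself is only partly seen, because the first three sessions precede the first FFMQ.

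**3. Can awareness alone produce the planned correlation?**
Simulation of the MBCT arm, 20,000 runs, with no true mindfulness–stress link. A shared reporting factor S explains a share s of the variance of each measure: FFMQ = √(1−s)·e₁ + √s·S and PSS = √(1−s)·e₂ − √s·S, so the expected correlation is −s. Test: t = r√((n−2)/(1−r²)), two-sided 5%. The documents give no value for s, so the range 0 to 0.5 is an assumption. n = 50 is the full arm; n = 45 is 50 × 0.90, from the protocol's 10% attrition.

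| s | mean r (about) | significant, n = 50 | significant, n = 45 |
|---|---|---|---|
| 0 | 0 | 5% | 5% |
| 0.1 | −0.10 | 10% | 10% |
| 0.2 | −0.20 | 29% | 26% |
| 0.3 | −0.30 | 58% | 53% |
| 0.4 | −0.40 | 83% | 79% |
| 0.5 | −0.50 | 97% | 95% |

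A significant correlation in the hypothesised direction is therefore weak evidence against expectation unless s is known to be small.

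**The case against.** The strongest reply is that the protocol claims little. Its verb is to understand, it offers active components as an alternative to mediation, and the sentence sits in a limitations paragraph. The hypotheses and Data analysis plan set out only correlations, the hypotheses framing them as explaining change in the MBCT group, and no indirect effect is planned. Other features bear on non-specific effects: SIRE matches group size, duration and frequency, and assessors are blinded. The session-3 timing has a stated reason, namely that mindfulness was reported to rise after the mid-point.

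Much of this stands. A reader might infer that the protocol claims FFMQ will show freedom from awareness bias, or that it plans a formal mediation analysis. The text supports neither. But a mediating effect is still named as something to be understood from these data, and the *Thus* still presents the measurement as the response to the bias. The active control and blinded assessors do not blind caregivers who report their own stress and mindfulness. The timing rationale does not supply a pre-intervention value or any SIRE value. A separate analysis plan cannot help, because the data are not collected.

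Two further objections bear on the remedy, and both are fair. Measuring FFMQ in both arms leaves shared expectation in place. And with recruitment from May 2018 and a scheduled end in May 2019, T0 may be past for many or all participants.

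**Conclusion.** The point holds in a limited form. As written, the trial cannot estimate the effect of arm on mindfulness or any mediated effect: 0 of 50 SIRE caregivers have a mediator value, and no sample size changes that. The FFMQ group × time test contradicts the MBCT-only collection. The planned correlations are legitimate as exploratory description within MBCT, but they do not answer awareness bias.

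The identification result needs no assumption beyond the stated data collection. The indirect-effect range and the false-positive rates rest on assumed inputs and only illustrate the mechanism.

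A reader might go on to doubt the stress result. The documents do not support that on this ground: the PSS is measured in both arms, and its comparison does not need FFMQ.

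**What to change.** **Preferred.** Give the FFMQ-SF to both arms before randomisation and at T1 and T2, keeping the session-3 measure in MBCT if wanted. Run an exploratory mediation analysis using randomised arm, for example arm → FFMQ at T1 and FFMQ at T1 → PSS at T2, adjusted for baseline FFMQ and PSS, with a bootstrap interval for the indirect effect. State that shared expectation and mediator–outcome confounding remain. Where T0 can no longer be collected, collect T1 and T2 in both arms and say so.

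**If SIRE FFMQ is not collected.** Delete the reference to a mediating effect, report exploratory within-arm associations, and remove FFMQ from the between-group model in the Data analysis plan.

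**In either case.** Remove the *Thus* link in Limitations and state participant awareness as a remaining limitation.

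**Cost.** 50 × 3 forms in SIRE + 50 × 1 at T0 in MBCT = 200 short questionnaires at visits already planned, and slightly longer visits; the alternative costs wording only. With 45 completers per arm, a two-sample t test (two-sided 5%, 80% power) detects an FFMQ difference of about 0.60 SD before baseline adjustment. That sizes the arm → mindfulness path only and says nothing about power for the indirect effect, so the analysis should stay exploratory.

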## Conclusion

According to the recent systematic review, only a few clinical trials have reported a preliminary and short effect of mindfulness in the family caregivers of PWD. To meet the needs for the family caregivers of PWD, this proposed study has collected feedback from family caregivers of PWD and addressed the limitations (i.e., a low adherence rate) from previous studies by modifying the original MBCT protocol. The modified MBCT protocol aims to facilitate and support the family caregivers by cultivating a mindful attitude, empowering themselves to manage their stress, and promoting their resilience. The stress of family caregivers can last a long time, and hence examining the sustainable effects of the modified MBCT (i.e., a 6-month follow-up) is important. This study will also collect other important information on the intervention, including the participants’ adherence to mindfulness practices, level of mindfulness, and qualitative data for better understanding the active ingredients of the modified MBCT. The findings from this proposed randomized controlled trial could provide scientific evidence for the effectiveness of the modified MBCT for family caregivers of PWD. If significant benefits are found, the modified MBCT can be used as a standard supportive intervention for the family caregivers of PWD.

## Trial status

Recruitment commenced in May 2018, and the trial is scheduled to end in May 2019.

## Abbreviations

BPSD: Behavioral and psychological symptoms of dementia
BRS: Brief Resilience Scale
CESDS: Center for Epidemiologic Studies Depression Scale
FFMQ: Five Facet Mindfulness Questionnaire
HADS-A: Hospital Anxiety and Depression Scale-Anxiety
ITT: Intention-to-treat
MBCT: Mindfulness-based cognitive therapy
MBI: Mindfulness-based intervention
MBSR: Mindfulness-Based Stress Reduction
NPI-Q: Neuropsychiatric Inventory Questionnaire
PP: Per-protocol
PSS: Perceived Stress Scale
PWD: People with dementia
SF-12v2: Short-form 12-item health survey version 2
SIRE: Social interaction and routine education
ZBI: Zarit Burden Scale
